## Abstract

**Background:**

The rising prevalence of mental health concerns among students is prompting universities to explore innovative solutions to support student well-being. This paper describes the protocol for the development, implementation, and evaluation of a mobile app designed to address the mental health and wellness needs of students. This project employs a student-centered approach, partnering with students from the initial needs analysis through to the final design and implementation stages.

**Objective:**

The app aims to increase the use of campus resources that address student mental health and wellness by improving the awareness of these resources through user-designated preferences that are established on the initial use of the app and then iteratively refined as it is used. The app is linked to the campus student’s electronic health record so that health and wellness services can be coordinated and enhanced and the student journey to and through care become more seamless. The long-term objective is to leverage data from both the app and electronic health record to improve individual and population health for the entire campus.

**Methods:**

At the beginning of the project, a comprehensive logic model was created to outline the core inputs, activities, outputs, outcomes, and long-term impacts that were desired for the app. The model emphasized the integration of the app within existing campus mental health and wellness services and its potential to foster a culture of well-being across the university community. An evaluation plan was developed that incorporates both quantitative and qualitative methods through biannual assessments to track trends and app impact across campus in addition to feasibility, acceptability, and usability as well as its reach, effectiveness, and sustainability. Validated measures such as the Patient Health Questionnaire and Generalized Anxiety Disorder scale were selected to track changes in mental health and wellness, while custom surveys and analytics will gauge user engagement and satisfaction. New students, including freshmen, transfers, and first-year medical students, are invited to participate after giving informed consent. They receive compensation for their involvement in both quantitative and qualitative assessments.

**Results:**

As of March 2025, we have collected over 600 survey responses from freshmen, transfer, and medical students. A second survey round and additional focus groups are planned for April to May 2025. No analyses have been conducted yet. The findings from this project have the potential to inform similar efforts at other institutions and contribute to the broader field of digital mental health innovation and the development of well-being interventions tailored for young people.

**Conclusions:**

By leveraging digital technology and actively engaging students in supporting their well-being, this initiative represents an innovative user-centered approach to improve mental health and wellness support on university campuses.

**International Registered Report Identifier (IRRID):**

DERR1-10.2196/68368

## Introduction

Students in higher education are tasked with navigating a major life transition that can be incredibly challenging as they move away from home, manage higher academic demands, navigate new social environments, and take on more personal responsibilities for their daily lives [1,2]. These changes can lead to high levels of stress and the onset or exacerbation of mental health issues [3].

Research has shown that university students experience high rates of mental health concerns and reduced well-being. In a 2024 National College Health Assessment survey of 103,639 students at 154 institutions, over 20% of the undergraduate and 15% of the graduate student respondents reported experiencing serious psychological distress. Anxiety and depression are the most prevalent problems, with over 35% of the undergraduate and 33% of the graduate students reporting having anxiety, and over 26% of the undergraduate and 25% of the graduate students reporting depression as chronic conditions [4]. Other studies globally have reported similar rates of common mental health concerns among university students, including anxiety, depression, eating disorders, substance abuse, and self-harm/suicidal ideation [5-8]. Further, there is evidence that the COVID-19 pandemic and associated social restrictions and campus closures amplified these rates [9].

Concerningly, many students who are struggling do not seek help. Estimates suggest that only around 30%-40% of the university students with mental health needs actually receive treatment [7,10]. There are many barriers to accessing mental health and wellness services, including stigma, lack of awareness of available resources, financial constraints, and difficulty navigating the complex health care systems [11]. Even for those who do seek help, mental health and wellness resources in many university campuses are often overburdened and insufficient to meet student needs [12]. Counseling centers frequently report long waitlists, limited session caps, and inadequate funding and staffing [13]. These resource constraints make it challenging for counseling centers to provide high-quality, comprehensive care.

Addressing the mental health and well-being crisis on university campuses requires a multifaceted approach [14]. In addition to increasing staffing for on-campus counseling, colleges should also focus on implementing evidence-based prevention and early intervention programs. This could include initiatives to reduce stigma, educate students on mental health and wellness, and teach coping strategies [15]. Strengthening connections between campus mental health and wellness services and local health care providers in the community can also help expand care available to students. Digital technologies embedded into care pathways is a recognized sustainable way forward to build capacity for student well-being and mental health support and improve transition to and through support resources and services.

Ultimately, addressing student mental health and well-being is crucial not only for individual well-being but also for academic success and long-term outcomes [16]. By taking steps to better support the mental health and wellness needs of university students, institutions can foster healthier and more resilient campus communities.

In recognition of the growing mental health and wellness crisis among university students, many institutions of higher education have implemented programs and initiatives aimed at supporting student well-being. These efforts have ranged from expanding on-campus counseling services to implementing mental health and wellness education and prevention initiatives. One approach has been to increase the resources and staff available at university counseling centers. Many universities have hired additional counselors, psychologists, and psychiatrists to expand their clinical capacity and reduce long waitlists [13]. Some have also extended hours of operation or established satellite locations to improve accessibility. However, the demand for services often continues to outpace available resources, limiting the impact of these expansions. Moreover, students who utilize on-campus counseling and wellness services have improved mental health and well-being and academic outcomes, but the overall impact on the broader campus population has been more limited, with persistent unmet needs and disparities in both utilizing the available services and access to care [17].

Colleges have also worked to destigmatize mental health issues and encourage students to seek help when needed. Awareness campaigns, gatekeeper trainings, and peer-to-peer support programs have been employed to foster a more open dialogue around mental health on campus [7]. Although these initiatives have shown some promise in reducing stigma, evidences of their effects on the actual utilization of services have been mixed.

Beyond clinical services, many institutions have implemented upstream prevention and early intervention programs. These have included efforts to promote stress management, healthy coping strategies, and emotional regulation skills through workshops, courses, and web-based modules [15,18]. Some colleges integrate mental health and wellness screenings into routine health checkups to facilitate early identification and treatment of issues, but there is limited published evidence of the effectiveness of these initiatives.

Moving forward, a comprehensive, public health-informed approach will likely be needed to truly address the mental health and wellness crisis affecting university students. This could involve better integrating campus mental health and wellness services with on and off-campus health care providers, expanding preventive programming, and working to change campus cultures and norms around mental health and wellness. Sustained institutional commitment and investment will be crucial to the success of these efforts.

In recent years, approaches that link digital mental health interventions with wellness services have emerged as a promising approach to expand access and use of support services for university students [19-21]. These web-based and app-based tools offer a variety of self-guided well-being interventions, teletherapy services, and mental health education resources that can complement traditional in-person counseling [22].

The rapid growth of digital solutions has been driven in part by their potential to overcome key barriers that prevent students from seeking help, such as perceived stigma, time constraints, and transportation challenges [23]. Many digital platforms allow users to access services discreetly and conveniently from their own devices [24]. Studies have also found that students may be more willing to engage with mental health and wellness support delivered via technology compared to traditional in-person therapy [21].

Evaluations of digital mental health interventions and well-being programs geared toward university populations have generally found positive outcomes. For example, a meta-analysis of internet-based cognitive behavioral therapy interventions for anxiety among university students showed significant reductions in symptom severity compared to control groups [18]. Other research has linked the use of mental health and wellness apps to improve symptoms of depression, stress, and disordered eating among students [25].

However, the success of digital intervention tools has been tempered by some important challenges. Uptake and sustained engagement with these programs is often low, with many students downloading apps but then failing to use them regularly [24,26]. Concerns about data privacy and security with digital platforms limit the appeal for some users, and the recent proliferation of mental health and wellness apps has resulted in a crowded and unregulated market, making it difficult for students to identify high-quality, evidence-based options. Finally, the lack of interfaces that enable data exchange between these tools and campus health and counseling services hinders the ability to provide a continuum of care for students [21].

Moreover, Patrick et al [27] argue that traditional research methods and approaches to digital health interventions overall are inadequate for the increasingly data-rich environment of digital health. They propose an “agile science” approach that emphasizes rapid iteration, ongoing computational modeling, and iterative personalization that dynamically address the complexity inherent in human existence. This approach allows researchers and interventionists to move beyond static, descriptive theories toward dynamic, predictive models that can drive more effective and sustainable digital health solutions.

Therefore, moving forward, a more strategic and coordinated approach is needed that integrates digital mental health innovation with health and wellness services on university campuses to maximize the impact and more holistically address the well-being needs of student. To accomplish this, in January 2023, the Joan and Irwin Jacobs Center for Health Innovation at University of California San Diego (UCSD) Health, in partnership with UCSD’s Campus Health and Wellness program, began to develop an app and the supporting information technology platform, branded as Willo. This paper describes the approach taken to develop Willo and then focuses on the plan for implementation and evaluation.

## Methods

This protocol is reported in accordance with the SPIRIT (Standard Protocol Items: Recommendations for Interventional Trials) 2013 statement [28] (Multimedia Appendix 1).

### User-Centered Design Process

From its inception, the development of Willo was in co-partnership with students, recognizing that students would be their primary users and beneficiaries. The project team collaborated with students throughout the design process to ensure that the final product would be tailored to their specific needs, preferences, and challenges.

The process began with a comprehensive gap analysis, where students from diverse backgrounds were invited to participate in focus groups and individual interviews (Multimedia Appendix 2). These sessions explored students’ mental health and wellness needs, the challenges they face in accessing support, and the gaps they perceive in existing campus services. Students shared their experiences managing stress, symptoms of anxiety and depression, along with other wellness concerns, providing valuable insights into the priority need areas for additional support and informing and shaping the app’s features and overall value proposition.

As the design process progressed, students continued to play an active central role in refining the app’s features and functionality. Through surveys, usability testing sessions, and design workshops, students provided feedback on various prototypes and concepts. They helped prioritize the features that would be the most useful and likely to be used regularly, such as mood tracking, guided meditation exercises, or anonymous peer-support forums. Students also offered insights into potential barriers to app usage, such as concerns about privacy or stigma, which informed the development of user-friendly interfaces and confidentiality measures. By maintaining this student-centered approach throughout the design process, the team ensured that the resulting app would be not only evidence-based by using state-of-the-art privacy and technological features and evidence-based content but highly relevant and appealing to its intended user base. This student-centered methodology fostered trust and transparency while enabling rapid, iterative refinement of the platform through continuous end-user feedback and contributions.

### Design Process

We conducted iterative co-design studies with students and key stakeholders involved in student well-being, including care providers, clinical staff, and university administrators, to identify the critical challenges affecting student well-being. A recurrent theme across these sessions was the absence of a personalized, regularly updated medium through which students could effectively engage with available university resources. Although a range of services existed, participants emphasized the need for an integrated system to support continuous search, discovery, and engagement. In response, we conceptualized a resource aggregator that could centralize both static resources (eg, physical centers, institutional services) and dynamic offerings (eg, events) organized by the core dimensions of wellness and relevant thematic tags. These tags served as the foundation for tailoring resource recommendations to individual student needs and preferences. Figure 1 illustrates the Willow app interface screens.

**Figure 1 figure1:**
[figure not shown]
Willo app. From left to right: onboarding interface, main home screen, search and exploration interface, and a detailed view of an individual event or resource.

### Logic Model

Based on the best practices in program evaluation in public health [29], our process of evaluation began with the development of a logic model that established the key inputs, activities, outputs, and outcomes associated with the implementation and evaluation of our student mental health and wellness mobile app. A scientific advisory committee composed of students with lived experience, experts in student health and well-being, medicine, psychology, digital interventions, public health, and health services evaluation, was formed to provide input to the app development team on each component of the model and to recommend measurable outcomes for each that would help determine the effectiveness and feasibility of the app. The logic model highlights the multifaceted approach needed to drive positive impacts at both the individual and institutional level. The short, intermediate, and long-term outcomes reflect the iterative and sustained nature of effecting meaningful change in campus mental health and well-being (Figure 2).

The advisory committee also made recommendations about the resources and assets necessary for the successful implementation of the project. These inputs included funding from university administration and external grants and interdisciplinary stakeholders, including clinical psychologists, student health clinicians, computer and data scientists, and user experience designers. Further partnerships with campus counseling centers and other student support services and access to university student population and data were identified as critical.

The essential actions and processes that have been undertaken to achieve the project’s goals are to conduct user research and needs assessment with university students, design and develop a mobile app prototype with evidence-based features, implement pilot testing and iterative improvements based on user feedback, and promote app availability and usage through campus-wide marketing and education.

**Figure 2 figure2:**
[figure not shown]
Logic model. ACTRI: Altman Clinical and Translational Research Institute; CAPS: Counseling and Psychological Services; H&W: Health and Wellness; R&D: Research and Development; UC: University of California; UCSD: University of California San Diego.

The immediate, tangible output of the project activities will include a fully functional mobile app for student mental health and wellness support, an increased awareness and utilization of campus mental health and well-being resources, and outreach and education for campus service providers to familiarize them with the app. The committee made recommendations about the following short-term, intermediate, and long-term changes to be assessed as a result of the project and how these lead to broader systemic change.

The short-term outcomes include improved mental health and wellness literacy and help-seeking attitudes among students, increased engagement with evidence-based self-management strategies, and enhanced feelings of social connectedness and reduced isolation.Intermediate outcomes include reduced symptoms of anxiety, depression, and other common mental health issues and increased utilization of the app and on-campus counseling and support services.Long-term outcomes are expected to be a positive shift in the campus culture around mental health and well-being; sustainable adoption and integration of the app through students; and improved overall student health, satisfaction, and success outcomes.The broader systemic changes that the project aims to contribute to over time would be a healthier and more resilient university student population, leading to reduced mental health–related costs and productivity losses for universities.

The committee emphasized the importance of viewing this logic model as a dynamic framework, subject to refinement and adaptation, as new evidence emerges and the project evolves. They also stressed the need for rigorous evaluation at each stage to ensure that the project is meeting its intended goals and to inform continuous improvement efforts.

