For continuous quality improvement, we plan to regularly review the evaluation results with the project team to identify the areas for app refinement and programmatic enhancements and use data to secure continued funding and support for sustaining and scaling the app-based program.

This evaluation plan (Table 1) outlines a mixed methods approach to assess the student mental health and wellness app project on multiple levels—individual student outcomes, community reach and usage, operational feasibility, and long-term sustainability. The plan emphasizes the importance of utilizing evaluation findings to drive ongoing improvement and broader dissemination of effective practices. Rigorous data collection, analysis, and reporting will be critical to demonstrating the value of this initiative to university stakeholders and external partners.

The evaluation team designed a process to evaluate cohorts of the students biannually. This process enables the team to monitor trends and changes at the population level across campus and assess the outreach, effectiveness, and impact of the app. In the first cohort, students who are new to the campus (ie, freshman, transfer, and first-year medical students) will be invited to enroll in the assessments. They will be required to provide informed consent before participating and will be compensated for their time and engagement in the quantitative and qualitative assessments (Multimedia Appendix 3).

**Table 1 table1:** A summary of the evaluation plan for the mental health and wellness app (Willow).

Evaluation domains	Outcomes	Key performance indicators	Data sources and collection method
Campus services awareness, accessibility, and utilization	Improving access to mental health resources, improved efficiency of use of resources for individual psychological counseling, referral to the app by counseling and psychological services & health and wellness providers, improved utilization of on-campus services	Satisfaction, in-app services usage, Counseling and Psychological Services usage, effectiveness and relevance of the app, utilization of campus services	App analytics, in-app rating systems, in-app surveys and questionnaires, focus groups; interviews with counseling and psychological services & health and wellness providers

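### Total counseling usage has no clear direction of success; the access indicator should be service contact among students who screened positive at the start of the period

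*Protocol article*

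**What the plan says.** The abstract's Objective states the aim: "The app aims to increase the use of campus resources that address student mental health and wellness by improving the awareness of these resources". In the Logic Model section, the outputs described after Figure 2 include "an increased awareness and utilization of campus mental health and well-being resources", and the intermediate outcomes are "reduced symptoms of anxiety, depression, and other common mental health issues and increased utilization of the app and on-campus counseling and support services". So more use is a stated direction of success, next to fewer symptoms.

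In the Evaluation Plan, the first row of Table 1 gives these indicators: "Satisfaction, in-app services usage, Counseling and Psychological Services usage, effectiveness and relevance of the app, utilization of campus services". None is tied to need. The outcome column of that row also includes "improved efficiency of use of resources for individual psychological counseling", which could be met by fewer visits.

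The Introduction describes the gap in other terms: "Estimates suggest that only around 30%-40% of the university students with mental health needs actually receive treatment". That is a rate among students in need, not a rate among all students.

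Under Quantitative Analyses, engagement with support services is an independent variable, and the primary dependent variables are mental health and well-being scores.

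**The concern.** The problem the article sets out is unmet need, but the indicator it names is total use. Total use moves with how many students are unwell as well as with how easily they reach care. A rise may mean better access or a sicker student body. A fall may mean worse access or success on the symptom goal.

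The setting makes this a practical matter. The first cohort is students new to campus, and the Introduction says that this transition can start or worsen mental health problems. The assessments are a fall baseline and a spring follow-up of participants recruited through the app, and no unexposed comparison group is described that would separate rising need from better access. The Evaluation Plan also says that the data will support the case for continued funding, so a rise caused by worsening health could be reported as the app working.

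**Working it through.** The article states no utilization figure or target, so there is no figure of the plan's own to reproduce. Its power statement does not bear on this point.

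**Identity.** U = P × s + (1 − P) × q, where U is total counseling use, P the share of students in need, s the share of those in need who reach care, and q the share of students without need who use the service.

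**Inputs**
- s = 30% to 40%, from the Introduction; mid-point 35%.
- P = 35%, a proxy from the Introduction's figure for undergraduates reporting anxiety (given as over 35%).
- q = 0 at first, then 5% and 10%. The article gives no value, so these are assumed.
- The changes in P and s are assumed.

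**Results with q = 0**

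| Scenario | P | s | U |
|---|---|---|---|
| Baseline | 35% | 35% | 0.35 × 0.35 = 12.25% |
| Need down by a fifth, access unchanged | 28% | 35% | 0.28 × 0.35 = 9.8% |
| Need down by a fifth, access up 5 points | 28% | 40% | 0.28 × 0.40 = 11.2% |
| Need down by a fifth, access up 10 points | 28% | 45% | 0.28 × 0.45 = 12.6% |
| Need up by a fifth, access unchanged | 42% | 35% | 0.42 × 0.35 = 14.7% |

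In the third row both aims are met and use falls. In the last row health is worse, access is no better, and use rises. In the fourth row symptoms and use both move in the stated direction, so the two goals are compatible.

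**Break-even.** Use stays flat when the new s equals the old s divided by (1 − relative fall in need). For a 20% fall, s must rise from 30% to 0.30/0.80 = 37.5%, from 35% to 43.75%, or from 40% to 50%. Conversely, a rise in s from 30% to 40% offsets a fall in need of up to 1 − 0.30/0.40 = 25%.

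**Use without need**

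| q | Baseline | Both aims improve (P 28%, s 40%) | Health worsens (P 42%, s 35%) |
|---|---|---|---|
| 5% | 15.5% | 14.8% | 17.6% |
| 10% | 18.75% | 18.4% | 20.5% |

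The directions hold, though the fall shrinks as q grows.

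**When need is measured.** Suppose 100 students are in need at the start and 45 receive care. Of those 45, 20 recover; of the 55 untreated, 5 remit (all assumed). At the end, 25 treated and 50 untreated students are still above the cut-off. A rate among those in need at the end reads 25/75 = 33%, while the rate among those in need at the start is 45/100 = 45%. Conditioning on concurrent need therefore understates access, and does so more as care works better.

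**The case against.** A reader might infer that the plan contradicts itself, because fewer symptoms must mean less counseling. The document does not support that. Symptoms lower use only if the share reaching care stays fixed, and raising that share is what the app is for. On the article's own figure, 60% to 70% of need is unmet, so there is room for both to improve.

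A reader might also infer that the access aim cannot be answered at all. That too goes beyond the document. The survey battery in Table 2 holds PHQ-8, GADS-7, two barriers-to-care instruments and a resource-use measure, so rising use alongside worsening scores would be visible to anyone who looked at both.

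Three further points stand in part:
- The quoted outcome covers the app and support services as well as counseling. The app brings together events and wellness resources, and use of those need not fall as symptoms do. The identity fits counseling best.
- Table 1 is a summary. Its outcome column speaks of improved rather than increased utilization, its indicator cell gives no direction or denominator, and the logic model is described as open to refinement. A fuller plan may define a denominator.
- The size of any reversal depends on the changes assumed. With the treated share going from 35% to 45%, total use falls only if need drops by more than 1 − 0.35/0.45 = 22.2%.

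What remains is that the article itself states the direction of success and names plain counseling usage as an indicator. The planned model does not settle the matter, because service engagement enters it as a predictor and not as an outcome.

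**Conclusion.** The point holds in a limited form. As named, total counseling usage has no unambiguous direction: in the illustration it goes from 12.25% to 11.2% when symptoms and access both improve, and to 14.7% when health worsens with access unchanged. The signs follow from the identity. The sizes rest on a proxy for need, the mid-point of the Introduction's treated share, and assumed changes in both.

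The indicator also does not measure the gap that motivates the project, which is care among students in need. The data for a better indicator appear to be largely in the planned battery, so this is a cheap improvement and not a flaw that undermines the evaluation.

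**What to change.** In the intermediate outcome after Figure 2 and in the first row of Table 1, define the access indicator as follows: among students at or above a pre-stated screening cut-off on PHQ-8 or GADS-7 at the start of a period (the prior wave, not the concurrent one), the share who report any campus service contact during that period. Take contact from the Knowledge and Usage of Student Resources measure. The expected direction is up.

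- Count service requests or waitlisting only if that measure already captures them. Its items are not shown, and more than 600 first-round responses are already in.
- Report use among students below the cut-off separately.
- Keep total counseling usage as a descriptive figure with no direction of success, read alongside symptom change.

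The cost is rewording one outcome and one table row; the article reports that no analyses have been done. The downsides are a smaller denominator and dependence on students with linked consecutive waves. The Ethical Considerations section describes ID numbers based on order of completion, so the team should confirm that one ID carries across waves. The new rate separates access from the level of need. It does not by itself attribute a change in access to the app, since no comparison group is described.
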